### Sample size considerations

As this is an exploratory pilot study, sample size has been chosen based on feasibility with respect to time and funding. As such, 22 participants per group (allowing for a drop out rate of 10%) will aim to be recruited, giving an overall total of 44 participants. A full size trial requires a total of 88 participants (44 in each group allowing for 10% drop out).

### Planned statistical analysis

The primary feasibility outcomes for this study will be reported descriptively (e.g. %, mean (standard deviation)) for recruitment rate, number of eligible participants, drop-out rate, adherence to interventions, number of adverse events, and diary completion.

For secondary outcome measures, treatment effect sizes with 95% confidence intervals will be calculated to compare change between groups at 2 and 4 months. The *a priori* time of primary interest is 4 months. The end point for each participant will be at the completion of the study at 4 months. The suitability of each secondary outcome measures for use in the population will be assessed by the number of completed questionnaires and missing data at each time point.

Analyses will be conducted on a blinded, intention-to-treat basis where all participants randomized will be included. No data substitution will be applied to adverse event data. Analyses will be conducted under the guidance of a statistician. SPSS software (Version 23, SPSS Inv, Chicago, IL, USA) will be used to perform all analyses.

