**Methods/design:**

This phase II pilot clinical trial is designed as a randomized, single-blind, parallel group, two arm, superiority trial. The trial will recruit 44 participants from Queensland and Tasmania, Australia. Volunteers aged 40 years and over must have clinical symptoms and radiographic evidence of patellofemoral osteoarthritis to be eligible for inclusion. Those eligible will be randomized to receive either foot orthoses and prescribed motion control shoes, or prescribed motion control shoes alone, to be worn for a period of 4 months. The feasibility of a phase III clinical trial will be evaluated by assessing factors such as recruitment rate, number of eligible participants, participant compliance with the study protocol, adverse events, and drop-out rate. A secondary aim of the study will be to determine completion rates and calculate effect sizes for patient reported outcome measures such as knee-related symptoms, function, quality of life, kinesiophobia, self-efficacy, general and mental health, and physical activity at 2 and 4 months. Primary outcomes will be reported descriptively while effect sizes and 95% confidence intervals will be calculated for the secondary outcome measures. Data will be analysed using an intention-to-treat principle.

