### Objectives

The primary objective of this study is to establish the feasibility of a phase III randomized clinical trial to determine if customized foot orthoses worn in prescribed motion control footwear are superior to prescribed footwear alone, in individuals with PF OA over 4 months. Specifically, feasibility will be assessed by evaluating: (i) participant recruitment rate; (ii) the number of eligible participants; (iii) the willingness of participants to commit to the study protocol; (iv) optimal time frames for manufacture and provision of the interventions; (v) adherence to the interventions over the 4 months of the study; (vi) the number of adverse events; (vii) diary completion, and; (viii) drop-out rate.

The secondary objective of this study is to determine completion rates and calculate treatment effect sizes for patient reported outcomes assessing knee-related symptoms, function, quality of life, kinesiophobia, self-efficacy, general and mental health, physical activity, treatment satisfaction, treatment success, and self-reported recovery rate, at two and 4 months. Two measures, the change in average and worst knee pain rated on a visual analogue scale, and patient-perceived global improvement from the interventions, will form the primary outcomes for a phase III trial and will assist in sample size calculations.

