#### Secondary outcome measures

Secondary outcome measures for this pilot trial will focus on completion rates and missing data of patient reported outcomes to determine those to be utilized in the phase III trial. Patient reported outcomes will be administered at baseline, 2 and 4 months, and will evaluate dimensions of pain, symptoms, function and physical activity level, quality of life, kinesiophobia, self-efficacy, and general and mental health. In addition, five questions pertaining to treatment outcomes will be completed at 2 and 4 months (Questions 2–6 below).
*Knee pain severity* will be evaluated at baseline, 2 and 4 months on a 100 mm visual analogue scale anchored with no distress (0) and unbearable distress (10). Usual pain on movement in the previous week and worst knee pain during a nominated aggravating activity in the previous week will be assessed [30]. The VAS for usual and worst pain is reliable, valid and responsive to change in individuals with PF pain, with a change of 20 mm representing the minimal clinically importance difference (MCID) [30].
*Global rating of change* (GROC) will be evaluated at 2- and 4-month follow-up. Participants will be asked to rate their overall change in knee pain on a six-point Likert scale (completely recovered, much improved, improved, no change, worse, much worse). GROC has been used to evaluate outcomes in large clinical trials of PF pain and OA [10, 11, 13, 31].
*Satisfaction of treatment*. To rate participants’ satisfaction with treatment at 2 and 4 months, they will be asked to respond to the following questions using a 5-point Likert scale (very satisfied, somewhat satisfied, neither satisfied nor dissatisfied, somewhat dissatisfied, very dissatisfied):
1. *“Over the course of treatment for your knee pain, how satisfied were you with your overall treatment?”*

2. *“If you had to live with the symptoms you have right now, how would you feel about it?”*

*Success of Treatment*. Participants will be asked two questions related to their perception of treatment success at 2 and 4 months:
1. *“Overall, would you agree that the treatment you have received has been successful for your knee pain?”* (Yes/No)

2. *“If a good friend has the same knee pain as you, would you recommend the same treatment you received?”* (Yes/No)

*Self-Reported Rate of Recovery.* At 2 and 4 months, participants will be asked to provide a number from 0–100, in response to the following question:

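### The plan compares change between groups and names no baseline adjustment; adjusting for the baseline score would give tighter intervals and guard against chance imbalance at no cost

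*Protocol article*

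**What the plan says.** The analysis of the secondary outcomes is given in one sentence of the Protocol article, Planned statistical analysis: "treatment effect sizes with 95% confidence intervals will be calculated to compare change between groups at 2 and 4 months". The same section makes 4 months the time of main interest. The Abstract adds only that "effect sizes and 95% confidence intervals will be calculated for the secondary outcome measures". Neither place names a model or a covariate.

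The baseline values exist: "Patient reported outcomes will be administered at baseline, 2 and 4 months" (Secondary outcome measures). The Objectives section names "the change in average and worst knee pain rated on a visual analogue scale" as one of two measures intended as phase III primary outcomes and as help for the phase III sample size. The other is patient-perceived global improvement, which has no baseline.

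On size, the article plans "22 participants per group (allowing for a drop out rate of 10%) will aim to be recruited, giving an overall total of 44 participants", and "sample size has been chosen based on feasibility with respect to time and funding". Under Blinding and data collection, allocation is 1:1 from a random number table, with no stratification named.

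**The concern.** The ordinary reading of the sentence is a difference in mean change. Subtracting the baseline in full is the right correction only if a participant 10 mm higher at baseline is expected to be 10 mm higher at follow-up. With similar SDs at both times the expected carry-over is r × 10 mm. The remainder is regression to the mean, and an unadjusted change score counts it as treatment effect whenever the groups differ at baseline.

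Two uses of the estimates are exposed. The Objectives section feeds the pain results into phase III sample size planning. The Discussion makes larger trials conditional on point estimates that suggest benefit. A chance baseline difference can move the point estimate, and the SD of change can overstate the variability that a baseline-adjusted phase III analysis would face.

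**Working it through.** **Inputs from the Protocol article.** 22 per arm with 10% drop-out: 22 × 0.9 = 19.8, so about n = 20 evaluable per arm. Confidence level 95%. Minimal important difference on the pain VAS 20 mm. Entry requires at least 30 mm pain on aggravating activities. No power, SD or effect size is given for the 44 participants, so there is no calculation to reproduce beyond this drop-out step.

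**Assumptions.** SD s = 20 or 25 mm, equal at baseline and follow-up; r from 0.3 to 0.9.

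**Formulas.**
- Variance of change: 2s²(1 − r).
- ANCOVA residual variance: s²(1 − r²). In large samples, ANCOVA variance divided by change variance is (1 + r)/2.
- Half-width: t × √(2/n × variance), with 38 df for change and 37 df for ANCOVA. The ANCOVA variance is multiplied by 1 + 1/(2n − 4) = 1 + 1/36 for the cost of estimating the slope.

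**Worked case, s = 25, r = 0.5.**
- Change: variance 2 × 625 × 0.5 = 625; half-width 2.024 × √(0.1 × 625) = 16.0 mm.
- ANCOVA: variance 625 × 0.75 × 37/36 = 481.8; half-width 2.026 × √(0.1 × 481.8) = 14.1 mm.
- Ratio 1.138. Since 20 × 1.138² = 25.9, the gain is worth about 6 participants per arm.

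**Range (half-widths in mm).**

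| r | SD 20: change | SD 20: ANCOVA | SD 25: change | SD 25: ANCOVA | Change wider by |
|---|---|---|---|---|---|
| 0.3 | 15.1 | 12.4 | 18.9 | 15.5 | 22% |
| 0.5 | 12.8 | 11.3 | 16.0 | 14.1 | 14% |
| 0.7 | 9.9 | 9.3 | 12.4 | 11.6 | 7% |
| 0.8 | 8.1 | 7.8 | 10.1 | 9.7 | 4% |
| 0.9 | 5.7 | 5.7 | 7.2 | 7.1 | 1% |

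Simulation with 5,000 trials at each of r = 0.3, 0.5 and 0.7 gave the same 22%, 14% and 7%.

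**Unequal SDs.** If the entry rule makes the baseline SD 0.8 of the follow-up SD (k = 0.8), the large-sample width ratio is √[(1 + k² − 2rk)/(1 − r²)]. The excess is then 13%, 6% and 1% at r = 0.3, 0.5 and 0.7.

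**Chance imbalance.** The SD of the baseline difference between arms is s√(2/n): 20 × √0.1 = 6.3 mm at s = 20. A gap of 10 mm or more in either direction then has probability about 11% (10/6.3 = 1.58 standard errors). Given a baseline difference D, the change contrast shifts on average by −(1 − r)D. For D = 10 mm that is −7, −5 and −3 mm at r = 0.3, 0.5 and 0.7. ANCOVA is not shifted on average. A 5 mm shift is a quarter of the 20 mm important difference.

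**The case against.** The strongest reply is that the sentence names a contrast and not a model. Regressing change on group and baseline is also a comparison of change, and it gives the same treatment estimate and interval as ANCOVA on the follow-up score. A condensed article may leave covariates to an analysis plan that is not shown. This is fair, and it is why the point is an improvement to the stated method and not an error. It does not remove the point: the only contrast stated is read most naturally as unadjusted, and one clause would settle it.

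It is also true that under randomisation the change contrast is unbiased on average, so the imbalance argument is conditional on the baseline difference that occurs. The size of the gain rests on undocumented inputs and nearly vanishes at high r. The estimates are secondary in a feasibility pilot, and no test, power figure or go/no-go threshold depends on them. All of this limits the weight of the point.

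Two stronger readings are tempting and should not be drawn.
- A reader might infer that the baseline scores are thrown away. They are not: a change score uses each one, with its coefficient fixed. Against an analysis of follow-up scores alone (half-width 12.8 mm at SD 20), change is worse at r = 0.3 (15.1 mm), equal at r = 0.5 and better at r = 0.7 (9.9 mm).
- A reader might infer that anyone missing a visit is dropped, in conflict with "Analyses will be conducted on a blinded, intention-to-treat basis where all participants randomized will be included". The section does not specify a complete-case analysis. It rules out data substitution only for adverse events and does not say how missing outcome scores are handled. A repeated-measures model would itself still need at least one follow-up score per participant.

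**Conclusion.** The point holds as a no-cost improvement. As written, the plan compares change without naming baseline adjustment, and in a trial of this size with simple randomisation that is generally less precise than ANCOVA and open to chance imbalance. The loss in interval width is about 1% to 22% over r = 0.9 to 0.3, assuming equal SDs and 20 evaluable per arm, and less if the baseline SD is the smaller one. Both r and the SD are assumptions. The point covers only continuous outcomes with a baseline value. Global rating of change, satisfaction, treatment success, rate of recovery and PASS are asked only at follow-up and cannot be adjusted in this way. The feasibility outcomes and the planned number of participants are not affected.

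**What to change.** Under Planned statistical analysis, state that for each continuous outcome measured at baseline, the between-group difference at 2 and 4 months, with 4 months of primary interest, will be estimated with its 95% confidence interval from a model adjusting for the baseline score (ANCOVA or an equivalent repeated-measures model). Add that the SD and the baseline/follow-up correlation will be reported for each such outcome, so that phase III can be sized for a baseline-adjusted analysis. State that outcomes without a baseline are compared at follow-up. Adjustment for site is optional. The cost is wording only, with no new data or participants. The change should be recorded before any analysis by group.

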### Ancillary and post trial care

If participants experience an adverse event during the study, the trial investigators will arrange ancillary care with appropriate care providers. At the completion of the study, participants will be entitled to keep their allocated interventions. Participants who wish to obtain additional foot orthoses will be provided with a referral to a suitably qualified podiatrist, who will be provided with details of study foot orthoses design to facilitate replication of clinical benefits. All participants will be given a post-trial care pack, which details additional options for footwear and management of PF OA, such as physiotherapy. The primary investigator will be available via phone or email contact for any general enquiries regarding footwear or additional care post-trial.

### Dissemination of results

Results of this pilot trial, regardless of magnitude or direction of effect, will be presented in peer-reviewed journal articles and presented at national and international conferences. All participants will be provided with a summary of trial results via email or post.

## Discussion

Clinical guidelines prioritise conservative interventions as a first line treatment in knee OA management [52, 53]. As PF OA and PF pain in younger individuals may form a disease continuum [9], non-surgical interventions known to be effective in younger individuals with PF pain may also improve symptoms associated with PF OA. This has been demonstrated with multimodal physiotherapy [10]. Thus, it is plausible that foot orthoses, another effective intervention in PF pain [13], will also be effective in older people with PF OA [11].

This pilot trial protocol has been designed to optimize its scientific rigor by following SPIRIT guidelines and with reference to the CONSORT statement for pilot and feasibility trials [17, 18, 54]. Strengths of the trial design include randomized, concealed allocation of interventions, blinded data analysis, and the use of outcome measures with proven reliability and validity in PF pain, PF OA or general knee OA. Furthermore, we have selected interventions and outcome measures that are easily administered in a clinical setting, which improves the clinical applicability of study findings.

We have chosen to evaluate the effectiveness of customized foot orthoses for PF OA. This is on the basis that the older cohort targeted in this trial is expected to display a greater range of foot deformity and morphologies [20], which can be more readily accommodated with a customized orthoses base. This is in contrast to previous studies in PF pain in younger adults, which used prefabricated foot orthoses based on their cost effectiveness, clinical time constraints with regards to provision of devices, ease of standardization for a research setting, and wide availability [13]. However, increasing availability of computer-assisted design and manufacture of customized foot orthoses allows for more standardized adjustment of custom molded devices suitable for a research setting, as well as faster manufacturing times. This pilot trial will assist in determining time frames for provision of customized devices. Should point estimates of effects suggest positive short-term benefits of customized foot orthoses for PF OA, this trial will inform the conduct of larger RCTs with longer-term follow-up reflecting standard clinical practice (e.g. at least 12 months), and concurrent cost-benefit analyses.

Eligibility criteria for this trial do not require participants to have a particular foot type. While foot orthoses have traditionally been prescribed for conditions associated with excessive foot pronation, they have been shown to be effective in a range of foot types and conditions [13, 55, 56]. While the mechanism of effect of foot orthoses in PF pain is unclear, foot mobility rather than foot posture has better predicted outcomes with foot orthoses [57]. It is unknown as to what foot characteristics are associated with PF OA, and whether specific foot characteristics will predict outcome with foot orthoses. A recent review highlighted that with advancing age there is a decrease in foot mobility, strength and function [58]. Thus, the relationship between foot characteristics and foot orthoses outcomes in PF OA are likely to be different to younger individuals with PF pain. While this issue would benefit from investigation, individual differences in foot structure and mobility in this older cohort will be accounted for in this study by the use of customized foot orthoses.

Foot orthoses must be worn in footwear. Recent investigations into the effects of different footwear on pain and medial knee loads in individuals with medial TF OA concluded that personal footwear might have significant, potentially negative effects on knee loading and pain [28, 59]. Footwear features such as midsole density or flexibility alter the interface between the foot and the support surface, affecting both the proprioceptive input and structural support of the foot [29]. Clinical trials investigating the effect of foot orthoses on lower limb pathology must therefore consider the influence of the type of footwear worn on the stuctural support of the foot and the effect of the footwear on proprioception, as footwear has a significant effect on balance parameters and falls risk [29]. The decision to use the New Balance 857® motion control cross-trainer with foot orthoses in this study was based on its structural features, which were considered unlikely to influence the camber of the orthoses, while physically supporting the foot and providing a stable base of support to reduce risk of falls. By controlling for footwear, and using footwear as a comparator, this trial will be able to evaluate the effectiveness of customized foot orthoses, while reducing the potential influence of confounders such as footwear. This pilot trial will assist in determining participant compliance with footwear restrictions over 4 months to inform feasibility of footwear restrictions for longer term studies.

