**Discussion:**

The results of this pilot trial will help determine the feasibility of a phase III clinical trial investigating whether foot orthoses plus motion control footwear are superior to motion control footwear alone in individuals with patellofemoral osteoarthritis. A Phase III clinical trial will help guide footwear and foot orthoses recommendations in the clinical management of this disorder.

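### Feasibility is the primary aim, yet 95% intervals are planned only for the secondary outcomes, and the one stated condition for larger trials rests on efficacy point estimates

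*Protocol article*

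**What the plan says.** The Objectives section of the protocol article sets the aim: "The primary objective of this study is to establish the feasibility of a phase III randomized clinical trial". It then lists recruitment, eligibility, adherence, adverse events, diary completion and drop-out, among others, as the matters to assess.

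On analysis, the Planned statistical analysis section says "The primary feasibility outcomes for this study will be reported descriptively (e.g. %, mean (standard deviation)) for recruitment rate", and continues through the other feasibility measures. For the secondary outcomes the same section says "treatment effect sizes with 95% confidence intervals will be calculated to compare change between groups at 2 and 4 months". The abstract makes the same split in one sentence: "Primary outcomes will be reported descriptively while effect sizes and 95% confidence intervals will be calculated for the secondary outcome measures".

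On what follows from the pilot, the abstract says "The results of this pilot trial will help determine the feasibility of a phase III clinical trial". The only sentence with an if-then form is in the main Discussion: "Should point estimates of effects suggest positive short-term benefits of customized foot orthoses for PF OA, this trial will inform the conduct of larger RCTs". It goes on to specify longer follow-up (at least 12 months is the example) and cost-benefit analyses.

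On sizing, the Objectives section says that the pain VAS measures and patient-perceived global improvement "will form the primary outcomes for a phase III trial and will assist in sample size calculations". Sample size considerations gives 22 per group (44 in total) for the pilot and 44 per group (88 in total) for a full-size trial, both allowing for 10% drop-out.

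**The concern.** A pilot run to judge feasibility should report its feasibility results with their uncertainty, and its forward-looking statement should rest on those results. Here both are the other way round. Intervals are named for the secondary efficacy outcomes and not for the primary ones, and the single condition written for larger trials turns on efficacy estimates from a trial sized on time and funding.

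Two things are at stake. A bare percentage from 44 people may be taken as confirming a planning figure that it cannot confirm. And the condition for going further could be met, or missed, for reasons unrelated to whether the larger trial can be run. A related gap is that the Objectives section does not say which pilot quantity will feed the phase III sample size: the SD, the response rate or the observed effect.

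**Working it through.** **Inputs from the article.** 22 per group and 44 in total, 10% drop-out, full-size total of 88 (Sample size considerations); 1:1 allocation (Experimental design); 20 mm MCID on the pain VAS (Secondary outcome measures); at least 8 h of wear per day (Interventions).

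**Assumed or inferred.** Completers per arm, the VAS SD, correlations between outcomes, and the illustrative drop-out count. The article gives none of these.

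**1. The plan's own figures.** The 44 is a convenience size, and no alpha, power, effect or SD is given for the 88, so only the drop-out step can be checked.
- 22 × 0.9 = 19.8 and 44 × 0.9 = 39.6, so about 20 and 40 completers per arm.
- Working forwards, 20 × 1.1 = 22 and 40 × 1.1 = 44, which match the stated figures. Dividing by 0.9 gives 23 and 45, one more per arm.

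**2. A favourable sign under no effect.** If the true difference is zero, the estimate is symmetric about zero, so P(estimate favours orthoses) = 0.50. This holds at 20, 44 or 200 per arm. Because no outcome is named, take two outcomes with correlation ρ: P(both favourable) = 1/4 + arcsin(ρ)/(2π).
- ρ = 0.3: 0.30 for both, 0.70 for at least one.
- ρ = 0.8: 0.40 for both, 0.60 for at least one.

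The missing threshold is what makes the condition uninformative. With an assumed SD of 20 to 30 mm and 20 per arm, an estimate of 20 mm or more under no effect has probability of only 0.001 to 0.018.

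**3. What the sample size does affect.** The SE of a standardised difference is √(2/20) = 0.316. The 95% half-width is 1.96 × 0.316 = 0.62 (normal) or 0.64 (t, 38 df), so about 0.63. On the VAS with SD 20 to 30 mm, the half-width is 12.8 to 19.2 mm, against the 20 mm MCID. The chance of a wrongly unfavourable sign is Φ(−0.3/0.316) = 17% at a true d of 0.3, and Φ(−0.5/0.316) = 6% at 0.5.

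**4. Precision of a primary outcome.** Take 4 drop-outs in 44, p = 0.0909, z = 1.96.
- Wilson centre: (0.0909 + 3.84/88) / (1 + 3.84/44) = 0.124.
- Wilson half-width: 1.96 × √(0.0909 × 0.9091/44 + 3.84/(4 × 44²)) / 1.087 = 0.088.
- Interval: 3.6% to 21.2%. The exact (Clopper-Pearson) interval is 2.5% to 21.7%.

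An observed 9% is therefore compatible with about twice the planned 10%.

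**5. Consequence for the full-size total.** To keep 40 completers per arm at 21% drop-out: 40/0.79 = 50.6, so 51 per arm and 102 in total, against 88.

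**6. If the observed effect were the design effect** (the article does not say so). At a true d of 0.5, the middle 80% of observed values is 0.5 ± 1.28 × 0.316, or 0.09 to 0.91 (unrounded 0.0947 to 0.905). With n per arm ≈ 16/d², that spans about 20 to about 1,780 per arm.

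**The case against.** A reader might infer that the Discussion sentence is a go/no-go trigger, so that an infeasible trial with a lucky estimate proceeds and a feasible one with an unlucky estimate is dropped. The text does not support that. The sentence says the pilot will inform later trials, with longer follow-up and cost-benefit analyses. It does not say that an unfavourable estimate stops anything. The abstract separately ties phase III feasibility to recruitment, eligibility, compliance, adverse events and drop-out. This part of the objection stands, and the point is limited accordingly.

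A reader might also blame the 50% chance on the pilot's small size. That is wrong: it holds at any size. Size affects precision and the chance of missing a real effect.

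A third inference would be that phase III will be sized on the observed pilot effect. The Objectives section says only that the measures will assist, and an SD or a response rate fits that wording equally well. Step 6 therefore shows why the wording should be closed, not what the plan does.

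Finally, the descriptive summaries are introduced as examples, and formal progression thresholds may sit in a fuller protocol or analysis plan that is not shown. Their absence is not counted here. What remains is a choice the article makes twice, in the abstract and in the analysis section, to set descriptive reporting of the primary outcomes against intervals for the secondary ones. The publication commitment under Dissemination of results, which applies whatever the direction of effect, does not address either matter.

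**Conclusion.** The point holds in limited form. The analysis plan names intervals for the wrong tier of outcomes given the stated aim, and the only written condition for larger trials rests on efficacy point estimates without a threshold, an interval or a named outcome. Nothing in the pilot's conduct is invalidated; what is weakened is how its results can be used.

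The size is moderate. An observed drop-out near 9% would leave anything from about 4% to 21% open, which moves the full-size total from 88 to about 102 at the upper end. The efficacy estimates carry an uncertainty of about ±0.63 SD.

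The drop-out result rests on an illustrative 4/44. The total of 102 also rests on 40 completers per arm being the intended number, and the ±0.63 on about 20 completers per arm in the pilot; both counts are inferred from the 10% allowance. The VAS figures rest on an assumed SD of 20 to 30 mm. The 50% chance needs only a symmetric estimate and no true effect.

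**What to change.** 1. In Planned statistical analysis and the abstract, report each feasibility proportion, rate or mean with a 95% confidence interval (Wilson or exact for proportions). Read it against figures already in the article where they exist: 10% for drop-out, and the advised 8 h per day for wear.
2. Reword the Discussion sentence so that going on to a larger trial rests on the feasibility results. Present the efficacy estimates, with their intervals, as supporting information and not as the condition.
3. In Objectives, state that the pilot will supply the SD, with its uncertainty, and the response rates for sizing phase III. State also that the target difference will be fixed in advance, for example on the basis of the 20 mm MCID the article cites, and that the observed pilot effect will not be the design effect.

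The cost is some rewording and a few extra intervals on data already being collected, with no added participants or visits in the pilot. The drawback is that the drop-out result will look less reassuring than a bare percentage.
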